### 3. OBJECTIVES AND EXPECTED RESULTS

**Objectives and hypotheses of the study.** The overall objective of this study is to investigate, in 70-85-year-old community-dwelling sedentary men and women, whether the combination of physical and cognitive training has greater effects on walking speed than physical training only. The effects of the interventions on falls will also be investigated. The specific aims, hypotheses and justifications for the hypotheses are the following:

**MAIN AIM:** To investigate, in older community-dwelling sedentary men and women, the effects of a 12-month structured progressive physical and cognitive training program (PTCT) on walking speed and dual-task cost in walking speed compared to physical activity (PT) only.

**Hypothesis:** The PTCT will induce significantly greater benefits on walking speed than the PT only. Dual-task cost is smaller after the PTCT intervention than after the PT-only intervention.

**Justification:** The key determinants of safe walking (physical and cognitive function) are amenable to physical activity interventions even in old age. Cognitive training has beneficial effects on cognition and there is suggestive evidence that cognitive training may have beneficial effects on walking speed among older people. A training program targeting both the key determinants underlying safe walking is likely to induce greater benefits than a program targeting only one key determinant.

**SECONDARY AIM:** To investigate the effects of the PTCT program on rate of falls during 12-month intervention and a one-year follow-up in the target population compared to the PT only.

**Hypothesis:** The rate of falls will be smaller among the PTCT group than the PT group during the intervention and a one-year follow-up.

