#### 4. RESEARCH METHODS AND MATERIAL, SUPPORT FROM RESEARCH ENVIRONMENT

**Study design.** *This study is a parallel group single blinded randomized controlled trial (RCT) with two research arms; Physical Training (PT, control) and a combination of Physical and Cognitive Training (PTCT).* The use of randomization and pre- and post-intervention measurements ensure the internal validity of the study and enable causal conclusions between the interventions and the main outcome. The design controls for confounding factors present before the study (e.g. age and general health of the participants) and those occurring during the study (e.g. change in season, adaptation to the measurements and aging). The interventions will last for 12 months. Measurements will be organized at baseline and at 6 and 12 months. Falls data will be collected during interventions and during the one-year follow-up. The study protocol has been designed according to the current guidelines for RCTs and will be registered in the International Standard Randomized Controlled Trial Number Register (ISRCTNR).

**Participants and recruitment.** Community-dwelling sedentary 70- to 85-year-old men and women will be recruited from the Jyväskylä population register. Jyväskylä is the seventh largest city in Finland and its population is comparable to the general Finnish population. In 2014, 9 % (n=12 238) of all the inhabitants were 70-85-years-old. In other comparable sized cities in Finland, the percentage of 70- to 85-year-old inhabitants is ~10 %.

Participants will be recruited in two waves (WAVE1, n=155 and WAVE2, n=155 in **Table 3**) to overcome the challenges related to the measurement and training of 310 participants. In both WAVES, recruitment will start with an information letter sent to a randomly selected 4000 (1/3 of the population) persons. The letter will contain information about the study and the announcement to expect a phone call during the following week. Phone numbers will be collected from a nationwide database. Repeat phone

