**Sample size.** A priori sample size calculations are based on previously published and our own data on 10-m walking speed. Our own data (SCAMOB) give reason to expect a baseline mean level of 1.3 m/s (standard deviation of 0.36 m/s) in both groups. We expect the PT intervention to induce a 4 percentage point mean increase in both groups and a 6 percentage point higher mean in the PTCT group than PT group. The SD is expected to remain unchanged in both groups. The follow-up within-person correlation for the two measurements, obtained from SCAMOB, is estimated to be  $r=0.80$ , yielding 0.23 m/s as an estimate of the SD for change. Setting the significance level at 0.05 and power at 80 % for the group-time interaction favouring the PTCT vs. the PT group indicated that a sample size of 135 participants per group would be required. The power analysis was based on Diggle et al. (2002) and verified by a simulation study with Mplus-software version 7. Given an anticipated dropout level of 15 %, we decided to recruit 155 participants per group. A additional power analysis was calculated for the secondary outcome of falls rate based on recently published data and formulae in Zhu & Lakkis (2014) for negative binomial distribution outcomes (intercept: 0.56, dispersion 0.64). At 80 % power and with a total sample size of 270-310, depending on the dropout rate, it would be possible to detect a difference of 27-29 % in falls rate significant ( $\alpha=0.05$ ) between the PT and PTCT groups.

Our sample size calculations are conservative. For comparison, a recent meta-analysis reported the mean effect of multicomponent PT on walking speed to be 8%. The mean effect of CT on walking speed has been reported to be 11%. Moreover, in a recent two-year falls prevention study, a 30% difference in falls rate between the exercise and non-exercise control group was expected.

**Measurements.** *The main outcome of this study is 10-m walking speed.* Participants are asked to walk as fast as possible over the 10-m course. The time to complete the walk will be measured by photocells. Low walking speed is associated with e.g. increased risk for disability, cognitive impairment, institutionalization and falls. It has also been used to establish thresholds for community activities such as the ability to cross the street safely.

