*Secondary outcomes are 6-min walking distance, dual-task cost in walking speed and fall incidence.* In the 6-min walking test participants are encouraged to walk up and down a 20-m circuit for six minutes covering as much distance as possible. No verbal encouragement is provided during the test. Six minute walking test serves as a measure for community walking and it is associated with e.g. mobility limitation and disability. The visuospatial dual-task walking test will be adopted from that used by Menant et al. Participants are asked to walk at self-selected speed along a 20-m long walkway. After that they will be asked to walk the same walkway while performing a visuospatial cognitive task. Walking times will be measured by photocells and the difference between the two walks (dual-task cost) will be calculated. The visuospatial task involve a display with three boxes side by side labelled A, B and C. Participants are asked to visualize a star located in one of the boxes making three movements. Prerecorded instructions will deliver the random starting position and the direction of the three movements, i.e. left or right. The cognitive task instructions will be delivered continuously throughout the walking trial

through headphones. A new instruction will be delivered within a second of the participant answering the previous question. Participants will practice the visuospatial task carefully before the dual-task test. Fall incidence will be monitored by monthly diaries throughout the study. Phone interview will be used to ascertain further details of falls and injuries and to chase missing data as suggested by the Prevention Of Falls Network Europe. A fall is defined as an unexpected event in which the participant comes to rest on the ground, floor or lower level without overwhelming intrinsic or extrinsic cause.

*Overall health* including depression (Geriatric Depression Scale) and nutritional status (MNA-SF) will be assessed during a medical examination. To ascertain safe participation in the measurements and intervention, contraindications (ACSM guidelines) and acute conditions (blood count, CRP and Hb) will be assessed.

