**Statistical analysis.** The effects of the intervention will be assessed on the intention-to-treat principal using linear mixed models for continuous variables and by a general estimation equation for categorical variables. The primary outcome is tested for group-interaction over time using an interaction contrast ( $t_{\text{time} \times \text{group}} = \mu_{\text{BL,int}} - \mu_{\text{FU,int}} - \mu_{\text{BL,cont}} + \mu_{\text{FU,cont}}$ ,  $t$ : contrast test statistic,  $\mu$ : estimated marginal mean, BL: baseline, FU: follow-up, int: PTCT intervention, cont: PT control) in a linear model for longitudinal data accounting for within-person correlation and different variances at the two time-points. Negative binomial regression will be used to estimate the incident rate ratio for falls. The Cox proportional hazard regression model will be used to calculate hazard rates for fallers in both groups with PT as a reference. In addition, individual changes in the main and secondary outcomes observed during the study will be calculated and a reliable change index computed.

**Research material, materials management plan and confidentiality of data.** A quality assurance system will be set up. This includes a written standard operation procedure as well as periodical meetings and checks for monitoring the intervention and quality of data collection. The personnel performing the measurements and supervising the interventions will be carefully educated. Data will be collected by questionnaires, interviews, health examinations and laboratory tests. Interview-based data will be collected using computer-assisted personal interviewing (SPSS Data Entry Builder software, SPSS Inc). Each participant will be assigned an identification number. The identification -key will be in the possession of the research coordinator, research nurse and PI during the data collection and thereafter in the possession

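### The primary contrast is written for two time points with an undated follow-up, although three visits are scheduled: fit all three and name month 12

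*Protocol*

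**What the plan says.** - **Visits.** Protocol section 4, Study design: "Measurements will be organized at baseline and at 6 and 12 months".
- **Primary test.** Section 4, Statistical analysis, gives a single interaction contrast of estimated marginal means. Its terms are defined only as "BL: baseline, FU: follow-up, int: PTCT intervention, cont: PT control", with no month attached to FU. The model behind it is described as "accounting for within-person correlation and different variances at the two time-points".
- **General model.** The opening sentence of the same paragraph plans an intention-to-treat analysis "using linear mixed models for continuous variables and by a general estimation equation for categorical variables". It does not list the visits to be included.
- **Sample size.** Section 4, Sample size, also works from one pair of measurements, without dating the second.
- **Aim.** Section 3 makes a combined programme lasting 12 months the subject of the main aim, and names two outcomes for it: "on walking speed and dual-task cost in walking speed compared to physical activity (PT) only".
- **Outcome ranking.** Section 4, Measurements: "The main outcome of this study is 10-m walking speed". It continues: "Secondary outcomes are 6-min walking distance, dual-task cost in walking speed and fall incidence".

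**The concern.** The protocol does not simply leave the primary model for later. It writes out the contrast and describes the covariance, and what it writes fits two visits while its schedule has three. Two consequences follow.

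1. **Unused information.** In a two-visit model, a participant measured at month 6 and lost before month 12 contributes only the baseline value. If loss depends on the response seen at month 6, the model lacks the variable that explains the loss.
2. **An undated test.** Walking speed is measured at two follow-ups and the contrast names neither. An analyst could take month 6, month 12, or whichever looks better.

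Section 3 also names dual-task cost in the main aim and its hypothesis, while section 4 ranks it as secondary. That is a smaller wording conflict.

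**Working it through.** **Inputs from the protocol (section 4, Sample size and Randomization):** baseline mean 1.3 m/s; SD 0.36 m/s; within-person correlation 0.80; SD of change 0.23 m/s; a 6 percentage point advantage for PTCT; alpha 0.05; power 80%; 135 per group; 15% dropout; 155 per group recruited; equal allocation.

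**Assumptions, not in the protocol:** two-sided alpha; the 6 points taken of 1.3 m/s, so delta = 0.06 × 1.3 = 0.078 m/s; constant SD; and two correlation patterns for three visits, both with 0.80 from baseline to month 12. Pattern A has 0.80 between adjacent visits. Pattern B has √0.80 = 0.894.

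**Step 1: reproduce 135.** n = 2(1.960 + 0.842)² × SD² / delta².
- SD of change 0.23: 2 × 7.849 × 0.0529 / 0.006084 = 136.5, so 137.
- Unrounded SD, 0.36 × √(2 × 0.20) = 0.2277: 2 × 7.849 × 0.05184 / 0.006084 = 133.8, so 134.

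The stated 135 is reproduced. One-sided alpha gives 106 to 108 and does not reproduce it. The figure rests on one outcome, one follow-up and an unsplit 0.05, so dating the follow-up at month 12 leaves it unchanged.

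**Step 2: precision of the 12-month contrast, 155 per group, covariance taken as known.**
- *Complete data.* SE = 0.2277 × √(2/155) = 0.0259 with or without month 6. Power is 85.5% either way.
- *15% missing at month 12* (155 × 0.85 = 131.75 observed per group), *two visits.* Variance per arm = 0.1296 × (1 − 0.64)/131.75 + 0.1296 × (1 − 0.80)²/155 = 0.0003876. SE = √(2 × 0.0003876) = 0.0278; power 80.0%.
- *Three visits, all of the missing 15% seen at month 6, pattern A.* The residual fraction at month 12 given both earlier visits is 0.2889. Variance per arm = 0.1296 × 0.2889/131.75 + 0.1296 × 0.1111/155 = 0.0003771. SE = 0.0275; power 81.1%.
- *Same, pattern B.* Variance per arm = 0.1296 × 0.20/131.75 + 0.1296 × 0.20/155 = 0.0003640. SE = 0.0270; power 82.4%.
- *Only half of the missing 15% seen at month 6.* Power 80.6% (A) and 81.3% (B).

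The gain is therefore 0.6 to 2.4 power points.

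**Step 3: dropout that depends on the 6-month response.** Simulation of 1.5 million per arm, with correlations 0.85 between adjacent visits and 0.80 from baseline to month 12. Of each arm, 7.5 to 15% leave after month 6. Where leaving is selective, its log-odds rise by 0.5 to 1.0 per SD of poorer change at month 6. All of these settings are assumed. The true 12-month effect is 0.078 m/s.

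| Selective dropout | Two-visit estimate | Three-visit estimate |
|---|---|---|
| PTCT arm only | 0.082 to 0.093 | about 0.078 |
| Same in both arms | about 0.078 | – |

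The one-arm case overstates the effect by 0.082/0.078 − 1 = 5% to 0.093/0.078 − 1 = 19%. The symmetric case has essentially no bias.

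**Step 4: free choice of month.** In units of the variance, the 6- and 12-month changes have covariance 0.20.
- Pattern A: both change variances are 0.40, so the correlation is 0.20/0.40 = 0.50. The chance that at least one two-sided 0.05 test rejects under the null is 9.1%.
- Pattern B: the change variances are 2(1 − 0.894) = 0.211 and 0.40, so the correlation is 0.20/√(0.211 × 0.40) = 0.69. The chance is 8.4%.

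**The case against.** **The month is strongly implied.** The main aim concerns a 12-month programme, the intervention lasts 12 months, and Study design speaks of pre- and post-intervention measurement; month 6 is not post-intervention. Nothing proposes a primary test at month 6. This stands: the 8.4 to 9.1% describes what the wording would allow, not a planned procedure. But the contrast itself carries no date, and one word would settle it.

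**The 6-month data may well be used.** A reader might infer that the plan discards them. No sentence says so. Linear mixed models are planned for continuous variables without limiting the visits, and a baseline-to-follow-up contrast of marginal means can be taken from a three-visit fit. An analysis plan that is not shown may settle this. What remains is that the sentence specific to the primary outcome describes variances at two time points, and its literal reading is a two-visit model.

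**The bias depends on the scenario.** A reader might infer that the main result will be biased upwards. That needs selective loss in one arm only. The heavier PTCT schedule (2 to 4 supervised sessions a week against 1 to 2) makes differential loss conceivable, but the protocol gives no evidence for it. It also reports dropout below 10% in the group's earlier studies.

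**There is one primary outcome.** A reader might infer from the main aim that walking speed and dual-task cost are co-primary and that type I error is inflated across them. The document does not support this. Measurements names one main outcome and ranks dual-task cost as secondary, Statistical analysis refers to the primary outcome in the singular, and the sample size uses walking speed alone at the full 0.05.

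**Conclusion.** The point holds as a mismatch between the stated primary model and the visit schedule, with an improvement available from data the trial already plans to collect. The model is worded for two time points, three visits are held, and the follow-up month is not named.

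The size is modest: no gain with complete data, and 0.6 to 2.4 power points with 15% missing at month 12. The stronger argument is robustness. A three-visit likelihood model remains valid when loss depends on the observed 6-month response, whether or not that loss differs between arms; a two-visit model is exposed when it does differ. These figures rest on the assumed three-visit correlations and dropout mechanisms, not on protocol data. The sample size of 135 per group stands.

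Dual-task cost in the main aim is a wording conflict with its secondary rank. It does not make the primary outcome ambiguous.

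**What to change.** - In Statistical analysis, replace the two-time-point description with one linear mixed model fitted to baseline, 6 and 12 months, with visit-by-group terms and an unstructured covariance.
- Date the contrast: name the baseline-to-12-month group-by-time contrast in 10-m walking speed as the only primary test, and the 6-month contrast as supportive.
- In section 3, move dual-task cost from the main aim and its hypothesis to the secondary aims, to match Measurements.

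The cost is a few sentences. No visit, measurement or participant is added, and the sample size does not change.

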## 5. ETHICAL ISSUES

The study will be performed according to the guidelines of the Finnish Advisory Board on Research Integrity (<http://www.tenk.fi/en/frontpage>), good scientific practice and current legislation. The study protocol has been designed according to the current guidelines for RCTs. Application for ethical approval will be made to the Jyväskylä Central Hospital Board. An informed consent, explaining the details of the study, possible risks, and permission to use the data for research purposes, participants' right to decline to participate at any point, anonymity and confidentiality of the data will be signed by the subjects before the baseline measurements. ICMJE guidelines will be followed when reporting the research results.

## 6. IMPLEMENTATION: BUDGET, TIME SCHEDULE, DISTRIBUTION OF WORK

**Budget (see Table 2).** The salaries of the senior members are covered by their host institutes. The PI will spend 35% and the other senior researchers 5-15% of their working hours on this project. Travel costs include travel of participants to measurements and training, conference trips and research exchanges between the collaborating Universities. Funding will also be applied from the Ministry of Education and different foundations, if necessary. Funding for MEG/EEG recordings will be applied with this application, but funding for data analysis and reporting will be sought elsewhere.

**Table 2.** Summary of funding applied for.

| Purpose / year                               | 2016          | 2017           | 2018           | 2019           | 2020          | Total          |
|----------------------------------------------|---------------|----------------|----------------|----------------|---------------|----------------|
| Salaries:                                    |               |                |                |                |               |                |
| -Coordinator, NN, 28 person months (pm)      | 3 833         | 23 695         | 24 398         | 4 139          |               |                |
| -Post doc N.N, 31 pm                         |               | 8 025          | 33 058         | 34 048         | 11 543        |                |
| -Statistician, 1.2 pm                        |               | 613            | 1 578          | 1 626          |               |                |
| -Research assistants, NN, 28 pm              |               | 23 128         | 23 813         | 3 664          |               |                |
| -Research nurse, NN, 12 pm                   |               | 12 046         | 12 408         |                |               |                |
| -Training surveillance and instructors, 16pm |               | 13 671         | 14 081         |                |               |                |
| Indirect employee costs                      | 2 108         | 44 647         | 60 135         | 23 939         | 6 348         |                |
| University overhead                          | 5 585         | 118 275        | 159 303        | 63 417         | 16 818        |                |
| Fees for Physician and ICT technician        | 3 000         | 5 000          | 2 000          |                |               |                |
| Gym fee, materials, publications, MEG/EEG    |               | 24 000         | 27 000         |                |               |                |
| Travelling expenses                          | 4 500         | 3 000          | 2 000          | 5 000          | 2 000         |                |
| Grand total                           | 19 027 | 276 099 | 359 775 | 135 881 | 36 709 | 827 490 |
| Funding: Home institution (30 %)             | 5 708         | 82 830         | 107 933        | 40 764         | 11 013        | 248 247        |
| Funding: Academy of Finland (70 %)    | 13 219 | 193 269 | 251 843 | 95 117  | 25 696 | 579 243 |

**Time schedule.** For details, see **Table 3**. Briefly, if the decision for funding is positive, recruitment of research personnel and the planning and designing of the interventions will start in spring and continue during autumn 2016. Participants will be recruited in two waves during 2017. Interventions will take place during 2017-2018 and follow-up for falls will continue until 2020.

**Table 3.** Time schedule

| Year                                                                     | 2016                                                                               |                                                                                     | 2017                                                                                 |                                                                                     |       |       |                                                                                      | 2018  |       |       |                                                                                       |       | 2019 |  | 2020 |
|--------------------------------------------------------------------------|------------------------------------------------------------------------------------|-------------------------------------------------------------------------------------|--------------------------------------------------------------------------------------|-------------------------------------------------------------------------------------|-------|-------|--------------------------------------------------------------------------------------|-------|-------|-------|---------------------------------------------------------------------------------------|-------|------|--|------|
| Months                                                                   | 9 - 12                                                                             | 1 - 3                                                                               | 4 - 6                                                                                | 7 - 9                                                                               | 10-12 | 1 - 3 | 4 - 6                                                                                | 7 - 9 | 10-12 | 1 - 6 | 7-12                                                                                  | 1 - 8 |      |  |      |
| Recruitment and training of study personnel, organizing interventions    | [figure not shown] |                                                                                     |                                                                                      |                                                                                     |       |       |                                                                                      |       |       |       |                                                                                       |       |      |  |      |
| Recruitment of subjects, WAVE1 WAVE2                       |                                                                                    | [figure not shown] |                                                                                      | [figure not shown] |       |       |                                                                                      |       |       |       |                                                                                       |       |      |  |      |
| BL, randomization, WAVE1 WAVE2                             |                                                                                    | [figure not shown] |                                                                                      | [figure not shown] |       |       |                                                                                      |       |       |       |                                                                                       |       |      |  |      |
| Interventions and 6 and 12 month measurements, WAVE1 WAVE2 |                                                                                    |                                                                                     | [figure not shown] |                                                                                     |       |       |                                                                                      |       |       |       |                                                                                       |       |      |  |      |
| Follow-up for falls, WAVE1 WAVE2                           |                                                                                    |                                                                                     |                                                                                      |                                                                                     |       |       | [figure not shown] |       |       |       |                                                                                       |       |      |  |      |
| Data file construction and quality check                                 |                                                                                    |                                                                                     | [figure not shown] |                                                                                     |       |       |                                                                                      |       |       |       |                                                                                       |       |      |  |      |
| Data analysis and reporting                                              |                                                                                    |                                                                                     |                                                                                      |                                                                                     |       |       |                                                                                      |       |       |       | [figure not shown] |       |      |  |      |

